## Abstract

**Background:**

Improving outcomes after surgery is a major public health research priority for patients, clinicians and the NHS. The greatest burden of perioperative complications, mortality and healthcare costs lies amongst the population of patients aged over 50 years who undergo major non-cardiac surgery. The Volatile vs Total Intravenous Anaesthesia for major non-cardiac surgery (VITAL) trial specifically examines the effect of anaesthetic technique on key patient outcomes: quality of recovery after surgery (quality of recovery after anaesthesia, patient satisfaction and major post-operative complications), survival and patient safety.

**Methods:**

A multi-centre pragmatic efficient randomised trial with health economic evaluation comparing total intravenous anaesthesia with volatile-based anaesthesia in adults (aged 50 and over) undergoing elective major non-cardiac surgery under general anaesthesia.

**Discussion:**

Given the very large number of patients exposed to general anaesthesia every year, even small differences in outcome between the two techniques could result in substantial excess harm. Results from the VITAL trial will ensure patients can benefit from the very safest anaesthesia care, promoting an early return home, reducing healthcare costs and maximising the health benefits of surgical treatments.

**Trial registration:**

ISRCTN62903453. September 09, 2021.

**Supplementary Information:**

The online version contains supplementary material available at 10.1186/s13063-024-08159-w.

## Introduction

### Background and rationale {6a}

More than 1.5 million major non-cardiac surgeries are performed in the NHS each year, including a variety of procedures from cancer resections to orthopaedic surgery [1]. High-quality general anaesthesia is essential for patients undergoing major surgery. In the NHS, general anaesthesia is most often maintained with an inhaled volatile anaesthetic agent (e.g. sevoflurane, isoflurane) [2]. A commonly used alternative is to maintain anaesthesia using infusions of intravenous anaesthetic drugs (e.g. propofol, remifentanil), a technique termed total intravenous anaesthesia or TIVA. The two techniques have important differences in side effect profile [3, 4]. There is a distinct lack of data describing the benefits and harms of either technique in terms of important patient outcomes.

Whilst the clinical endpoint of general anaesthesia is broadly similar between inhalational anaesthesia and TIVA, their underlying pharmacological actions are very different. Propofol (an intravenous anaesthetic drug used to provide TIVA) and inhalational hydrocarbon-based anaesthetic gases are both recognised to mediate general anaesthesia via the GABA_A_ receptor in the brain, but it is increasingly understood that general anaesthesia is the product of action on many different neuronal receptors rather than via a single mechanism [5]. Both inhalational and TIVA agents have wide-ranging and differing interactions with a host of other molecular targets including potassium and voltage-gated ion channels and glycine receptors [5–7]. One of the suggested benefits of inhalational anaesthesia is suppression of pro-inflammatory mediators that reduce the systemic inflammatory response to the tissue injury caused by surgery [8–10]. In addition, animal studies and observational human studies suggest inhalational anaesthesia may have cardioprotective properties during surgery [11].

There is emerging evidence suggesting anaesthetic techniques may affect disease-free survival amongst patients undergoing cancer surgery. Surgical resection can provide complete removal of primary tumour and potential cure for many cancer patients. However, despite apparently complete tumour resection, disease progression can occur in up to a third of patients. There is some preclinical evidence indicating that the systemic inflammatory response and immune disequilibrium following surgery can allow growth of metastases [12, 13]. Small mechanistic studies have suggested TIVA can prevent immunosuppression and inhibit cancer cell migration [13, 14], but clinical studies have so far not demonstrated any benefit of anaesthetic techniques in cancer outcomes following surgery [15].

Our literature review found 11 systematic reviews and five Cochrane reviews that compared different aspects of intravenous and inhalational anaesthesia. Two systematic reviews which examined the impact of anaesthetic techniques on long-term cancer outcomes suggested with low certainty that TIVA may be beneficial [16, 17]. Two systematic reviews compared complications and mortality of anaesthetic techniques in patients undergoing cardiac surgery and found no differences in peri-operative complications or survival [18, 19]. Eight other systematic reviews compared anaesthetic techniques in selected surgical groups: neurosurgery [20, 21], one lung ventilation in thoracic surgery [22], robotic assisted laparoscopic surgery [23], paediatric surgery [24, 25], ambulatory/day case surgery [25, 26]. The findings suggest TIVA is associated with faster recovery of consciousness, a reduced risk of nausea and vomiting and less pain immediately after surgery [27–29]. A 2018 Cochrane review suggests a reduced risk of post-operative cognitive dysfunction for older patients undergoing non-cardiac surgery with TIVA, but uncertainty remains due to high risk of bias in included studies [30]. Crucially, these systematic reviews did not provide evidence on patient-centred outcomes or safety outcomes such as accidental awareness during anaesthesia. We identified only one large randomised trial in non-cancer patients that compared TIVA with volatile-based anaesthesia in cardiac surgery: the MortalitY in caRdIAc surgery trial (MYRIAD), which included 5400 patients undergoing cardiac surgery who were randomised to TIVA or inhalational anaesthesia. This trial was designed to specifically test whether inhalational anaesthesia was protective against myocardial injury and reduced mortality in patients undergoing cardiac surgery [31]. The trial was stopped early for futility with similar 1-year mortality rates in both groups.

The choice of anaesthesia not only affects the care of patients during surgery but may also impact on their quality of recovery, survival and other patient safety outcomes, including accidental awareness under anaesthesia. Prompt recovery and discharge from hospital will enhance physical recovery, limiting immobility and physical deconditioning [32, 33]. These aspects are of growing importance as frail older patients now undergo major surgery more often than ever before [34, 35].

### Objectives {7}

The primary objective of this trial is to test whether TIVA is superior to inhalational anaesthesia in terms of days alive and at home at 30 days (DAH30), survival and quality of recovery amongst patients undergoing major non-cardiac surgery. Secondary objectives are to evaluate the safety of TIVA, including post-operative complications and incidence of accidental awareness under anaesthesia; and to assess the cost-effectiveness of TIVA.

### Trial design {8}

An open-label multi-centre pragmatic efficient randomised (1:1) superiority trial comparing TIVA and volatile-based anaesthesia in adults aged 50 years and over, undergoing elective major non-cardiac surgery under general anaesthesia with health economic evaluation. The VITAL trial uses an efficient trial design partnering with an existing national cohort study hosted by the Royal College of Anaesthetists: the Perioperative Quality Improvement Programme, PQIP (pqip.org.uk). PQIP has been running successfully since 2017, providing a database of patient outcomes to facilitate benchmarking and quality improvement in perioperative care [36]. VITAL will be nested within PQIP study and utilise existing PQIP database, data collection and follow-up procedures.

Within VITAL, a small qualitative study will be undertaken to examine ways of consenting participants into complementary studies. The study will consist of interviews with participants of VITAL, patients who declined to take part in VITAL and staff members involved in consenting participants into the trial. Potential participants will be contacted by a trained qualitative researcher for their consent to take part in a semi-structured interview exploring their experiences.

## Methods: participants, interventions and outcomes

### Study setting {9}

Patients were under the care of participating surgical and anaesthetic care teams in at least 40 NHS hospitals from England, Wales and Scotland participating in PQIP.

### Eligibility criteria {10}

Participants are eligible to be included in the trial if they meet the following criteria:

Inclusion criteria.Age ≥ 50 yearsElective major non-cardiac surgery under general anaesthesia (as per PQIP inclusion criteria)Written informed consent for trial participation

Exclusion criteria.Known contraindication to either TIVA or inhalational anaesthesiaClinician refusalProcedures where the participant is not expected to survive for 30 daysPrevious participation in VITAL trialParticipant unable to give informed consent or complete questionnaires

### Who will take informed consent? {26a}

Potential participants will be screened by research staff at the site having been identified from pre-admission clinic lists, operating theatre lists and by communication with the relevant nursing and medical staff. Before surgery, potential participants will be identified and approached by a member of the research team. This may be conducted via telephone, post, online or face-to-face consultations and provides an opportunity for the research team to explain the trial to the participants in detail. Participant information sheets can be posted or emailed to potential participants for their perusal and consideration. The participant will be approached prior to surgery at the first suitable opportunity to allow time for any questions. It is recommended (although not mandated) that the participant is approached at least 1 day prior to the date of surgery. Written informed consent must be obtained before surgery and can be obtained using either paper or electronic systems depending on individual site arrangements.

### Additional consent provisions for collection and use of participant data and biological specimens {26b}

Not applicable, no biological specimens are collected.

## Interventions

### Explanation for the choice of comparators {6b}

General anaesthesia is most often maintained with an inhaled volatile anaesthetic agent (e.g. sevoflurane, isoflurane) [2]. A commonly used alternative is to maintain anaesthesia using infusions of intravenous anaesthetic drugs (e.g. propofol, remifentanil), a technique termed total intravenous anaesthesia or TIVA. The two techniques have important differences in side effect profile.

## Intervention description {11a}

### Total intravenous anaesthesia (TIVA)

Participants randomised to the TIVA arm of the trial will have their anaesthesia maintained with intravenous anaesthetic agents as determined by the treating anaesthetist. The administration of TIVA will not be protocolised and will be left to clinical discretion for management. Maintenance of general anaesthesia should be via TIVA only. Clinicians are reminded to avoid volatile-based inhalational anaesthetic agents in this participant group.

### Volatile-based inhalational anaesthesia (INH)

Participants randomised to the INH arm of the trial will have their anaesthesia maintained with inhalational volatile-based anaesthetic agents as determined by the treating anaesthetist. Administration of INH will not be protocolised and will be left to clinical discretion for management. Maintenance of general anaesthesia should be via inhalational route only. Clinicians are reminded to avoid intravenous anaesthetic agents in this participant group.

### Criteria for discontinuing or modifying allocated interventions {11b}

It is possible that the participant may receive an anaesthesia technique other than the one that was allocated to them within the trial, for example due to equipment malfunction or change in clinical circumstances. In this pragmatic trial, brief deviations or interruptions in the allocated anaesthesia technique lasting shorter than 20 min will not be interpreted as true cross over between treatment arms.

### Strategies to improve adherence to interventions {11c}

Site teams are trained on trial protocol during site initiation visits and regular updates are provided during site team catch-ups and newsletters. Protocol deviations will be monitored throughout the trial by the trial management group and data safety and monitoring committee. Where deviation rates appear excessive, contact will be made with site investigators to provide retraining and support.

### Relevant concomitant care permitted or prohibited during the trial {11d}

Anaesthesia will be administered by experienced anaesthetists and delivered according to local guidelines. All other participant care will be conducted as per routine clinical practice and information collected in trial case record forms.

### Provisions for post-trial care {30}

The clinical interventions used in the trial are performed at a single point in time and cannot be amended in any way once performed. Both interventions are routinely used in clinical practice. As such, there is no need to provide continuing post-trial care other than as standard local practice. Post-operative complications will be managed as per routine care at participating sites.

## Outcomes {12}

### Effectiveness

#### Primary outcome

The primary outcome is days alive and at home at 30 days after surgery (DAH30). This sensitive measure reflects the number of days from surgery to discharge and also any hospital readmission(s) during that month as well as survival.

#### Secondary outcomes

▪ Days alive and at home at 90 days (DAH90)▪ 30-day and 90-day mortalities▪ Six-month mortality▪ Quality of recovery after anaesthesia (QoR-15) at day 3 after surgery [37]▪ Patient satisfaction with anaesthesia (Bauer questionnaire) on day 1 after surgery [38]

### Safety

Accidental awareness under anaesthesia (modified Brice questionnaire) on day 3 and 30 days after surgery [39]Major post-operative complications Clavien-Dindo grade 2 and above within 30 days after surgery [40]

### Health economics

Health resource use during the 6 months after surgeryHealth-related quality of life evaluated using EuroQoL instrument (EQ-5D-5L) at baseline, at hospital discharge, at 30 days and 6 months after surgery [41, 42]

### Participant timeline {13}

**Table Taba:** 

**Visit window**	**Day 0 Baseline**	**Day 1**^**#**^	**Day 3**^**#**^	**Day of discharge**^**#**^	**Day 30 + 7 days**	**Day 90 + 7 days**	**6 months** ± 21 days
Informed consent	√						
Medical history	√						
Inclusion/exclusion criteria	√						
Surgical speciality	√						
Expected duration of surgery (< 2 h, ≥ 2 h)	√						
Cancer surgery/non-cancer surgery	√						
Preoperative frailty (Rockwood frailty score)	√						
Intervention	√^						
Bauer questionnaire		√^					
QoR-15			√^				
Modified Brice questionnaire			√		√		
Post-operative delirium (4AT)			√				
Post-operative complications (Clavien-Dindo grade II and above)					√^		
Length of stay*				√^			
Survival status*					√^	√	√
Hospital readmission*					√	√	√
Health resource use							√
Quality of life EQ 5D	√^			√^	√^		√^

*Information needed for DAH30 and DAH90

^Already collected by PQIP database

^#^Or closest next working day

### Sample size {14}

The total sample size will be 2500 participants over the two intervention arms (1250 per arm). The primary endpoint of this trial is the number of days alive and at home 30 days after surgery (DAH30). DAH30 is a continuous number between 0 and 30 which reflects, out of the 30 days following surgery, the total number of those days that a participant spends alive and at home [43]. In this definition, home reflects any place other than hospital. If a participant dies within those 30 days, their value is set to 0. The secondary endpoints of this trial include number of days alive and at home 90 days after surgery (DAH90) and survival at 90 days after surgery. The population eligible for entry into VITAL is similar to those participants undergoing elective surgery reported by Bell in 2019 with a mean DAH30 of 25 (SD 6.6) [44]. Applying the VITAL trial inclusion and exclusion criteria to sample data using hospital episode statistics, we found a mean DAH90 of 72.9 (SD 21.3) and a 90-day mortality rate of 3.8%. We have adopted a conservative estimate of 7.5 for the standard deviation of DAH30 and a conservative estimate of 22 for the standard deviation of DAH90. With a 5% two-sided significance level and 90% power, the randomisation of 2500 participants (1:1) to either TIVA or inhalational anaesthesia would allow detection of a difference of 1 day in DAH30 between treatment arms. This sample size allows for up to 5% loss-to-follow-up. Also, with a 5% two-sided significance level, this 2500 participant sample will allow us to detect a difference in DAH90 between arms of 3 days with 90% power, or 4 days, with > 95% power. For a safety non-inferiority analysis of 90-day mortality, assuming there is truly no difference between modes of anaesthesia (3.8% mortality), a 2500 participant sample would provide 80% power for a one-sided 95% confidence interval to exclude a 1.9% increase in mortality due to TIVA (a relative risk of 1.5). A one-sided 97.5% confidence interval would exclude an increase due to TIVA of 2.2% (a relative risk of 1.6).

### Recruitment {15}

Participants will be recruited from at least 40 UK hospital sites with a track record of active and successful recruitment to clinical trials and an appropriate patient case mix.

## Assignment of interventions: allocation

### Sequence generation {16a}

Participants will be randomised on a 1:1 basis to receive either TIVA or inhalational anaesthesia. Randomisation will be undertaken through a simple and secure, Interactive Voice Response Randomisation System (IVRS) that has been established by the programming team at Warwick Clinical Trials Unit. This computerised procedure will use a minimisation algorithm to ensure balance in treatment arm allocation across the following four stratification variables, factors thought to affect outcome either through treatment effectiveness or underlying prognosis, also permitting appropriate exploratory subgroup analyses:Surgical speciality (musculoskeletal/intra-abdominal/thoracic/vascular/other)Expected duration of surgery (< 2 h, ≥ 2 h)Cancer surgery/non-cancer surgeryPreoperative frailty (Rockwood frailty score)—well/vulnerable/frail [45]

### Concealment mechanism {16b}

Allocation concealment will be ensured as the IVRS at the WCTU will not release the randomisation code until the patient has been recruited into the trial.

### Implementation {16c}

Recruiting centres will be asked to randomise participants on the day of surgery, once the planned surgery is confirmed as taking place. There will be occasions when surgery is cancelled at the last minute and rescheduled to another day. If the participant is happy to remain in the trial, recruiting centres will be asked to inform the VITAL team at WCTU of the new surgery date as soon as possible, and data collection timepoints will be adjusted. Participants should receive their original allocated intervention at their new scheduled surgery date. If the surgery is cancelled indefinitely, or the participant is no longer suitable for the trial, the recruiting centre will be asked to inform the VITAL team at WCTU as soon as possible.

## Assignment of interventions: blinding

### Who will be blinded {17a}

In this trial, it is not possible to blind participants or the research staff at sites to a participant’s randomised allocation. The primary outcome and most of the clinically reported secondary outcomes are objective. During the trial, the trial management group and the trial steering committee will not see outcome results broken down by treatment arm.

### Procedure for unblinding if needed {17b}

Not applicable; VITAL is an open-label study.

## Data collection and management

### Plans for assessment and collection of outcomes {18a}

Participants will be contacted by telephone at day 30 (+ 7 days) by site research staff to screen for late recall of accidental awareness and collect data on EQ-5D-5L, hospital readmission and any post-operative complications that are classed Clavien-Dindo Severity Grade II or above. Day 90 (+ 7 days) follow-up will be completed by a check of medical records only. Participants will be contacted by telephone at 6 months post-surgery (± 21 days) by site research staff to collect data on health resource use based on participant diary and quality of life using EQ-5D-5L.

Modified Brice Questionnaire is used to screen for recall of accidental awareness under general anaesthesia (AAGA). A potential case of AAGA should be flagged by the local research team if a participant responds that they remembered something between going to sleep and waking up or they answered ‘Awareness’ to the question asking them to report the worst thing about their operation. The principal investigators for each of these participants should be contacted by the local research team and asked to give their opinion of the likelihood of AAGA for their participants as ‘probable’, ‘possible’, ‘unlikely’ or ‘un-assessable’ according to previously defined criteria and using available local data. All cases of probable and possible AAGA should be reported to WCTU by completion of the Brice Questionnaire Additional Data Form. Participants should be followed up locally as per usual care.

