## Statistical methods

### Statistical methods for primary and secondary outcomes {20a}

All statistical analyses will be undertaken on an intention to treat basis where possible to preserve randomisation, avoid bias from exclusions and preserve statistical power. Hence, all participants randomised into the trial, regardless of whether they received their randomised intervention, will be analysed according to their randomised group using data collected up to their final follow-up in the trial (6-month timepoint or the last timepoint prior to their withdrawal or loss to follow-up). We will do an additional per-protocol analysis including only participants who received their allocated intervention (as detailed in the statistical analysis plan). Participants not receiving surgery or withdrawing consent for follow-up prior to surgery will not be included in relevant denominators.

For the primary outcome of DAH30, each randomised treatment arm’s point estimate (and 95% confidence interval) will be reported. In addition, DAH30 will be compared across randomised treatment arms using independent samples *t*-tests, Wilcoxon rank sum tests or appropriate modelling techniques depending on the distribution of the data. The secondary outcome of DAH90 will be analysed as per the DAH30 techniques. Rates of mortality and major post-operative complications will be assessed across randomised arms using chi-squared tests, with logistic regression used to adjust for stratification variables.

Quality of recovery, participant satisfaction and accidental awareness will be scored using appropriate manuals.

The four stratification factors used at randomisation define sub-groups of interest.Surgical speciality* (intrabdominal/musculoskeletal/thoracic/vascular/other)Expected duration of surgery (< 2 h, ≥ 2 h)*Cancer surgery/non-cancer surgery*Preoperative frailty (Rockwood frailty score*)—well/vulnerable/frail [45]

A Consolidated Standards of Reporting Trials (CONSORT) flow diagram will be produced, showing the frequency of participants:Assessed for eligibilityExcluded prior to randomisation (and the frequency of each reason for exclusion)RandomisedAllocated to each randomisation armReceiving or not receiving their randomised treatmentFollowed-up at each protocol specified timepointLoss to follow-up at each protocol specified timepoint (and the frequency of each reason for loss to follow-up)

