### Adverse event reporting and harms {22}

VITAL is a non-CTIMP trial and all trial interventions are already in routine clinical use for participants undergoing major non-cardiac surgery. Expected post-operative complications (starting from end of surgery on day of surgery to 30 days post-surgery) will be collected as a trial outcome and will not be recorded separately as AEs. These events will be included as part of the safety analysis for the trial and therefore do not need to be reported separately to the trial coordinating centre. No additional AEs will be collected, other than those specified as post-operative complications (Additional file 1: Appendix). Post-operative complications will be reviewed/monitored at intervals by the DMC.

Beyond these defined, expected complications, adverse events will be reported in accordance with the UK Policy Framework for Health and Social Care Research, the Principles of GCP as set out in the UK Statutory Instrument (2004/1031; and subsequent amendments) and the requirements of the Health Research Authority (HRA). When completing an SAE form, the principal investigator or medically qualified delegate will be asked to define the causality and the severity of the SAE. On receipt of an SAE form at the trial office, the chief investigator or delegate will independently determine causality of the SAE. An SAE judged by the PI, CI or delegate(s) to have a reasonable causal relationship with the intervention will be regarded as a related SAE. The CI or delegate(s) will assess all related SAEs for expectedness. If the event is unexpected, i.e. is not defined in the protocol as an expected event, it will be classified as an unexpected and related SAE.

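### Accidental awareness is rated by a site investigator who is not masked to the arm, and supporting detail is specified only for cases that investigator rates probable or possible

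*Protocol article*

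**What the plan says.** Awareness is a named target of the trial. The secondary objectives cover safety, "including post-operative complications and incidence of accidental awareness under anaesthesia" (Objectives, 7). The first entry under Safety is "Accidental awareness under anaesthesia (modified Brice questionnaire) on day 3 and 30 days after surgery".

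Section 18a sets out how a case is established:

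1. The local research team flags a potential case from two fixed Brice answers: remembering something between going to sleep and waking, or naming awareness as the worst thing about the operation.
2. The site principal investigator is then "asked to give their opinion of the likelihood of AAGA for their participants". The rating is probable, possible, unlikely or un-assessable, and it uses previously defined criteria and whatever local data are available.
3. "All cases of probable and possible AAGA should be reported to WCTU by completion of the Brice Questionnaire Additional Data Form". Nothing is said about a form for the other two ratings.

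On blinding, section 17a states that "it is not possible to blind participants or the research staff at sites to a participant’s randomised allocation". It adds that "The primary outcome and most of the clinically reported secondary outcomes are objective". No masked or central reading of awareness cases is described.

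**The concern.** The flag is mechanical, but the step that follows is a judgement. It is made at a site where allocation is known, from local data that nothing in the article masks. The predefined criteria narrow the discretion without removing it, particularly at the border between possible and unlikely.

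That border also decides whether an Additional Data Form is specified. The cases most in need of a second look, those flagged by rule and then rated down, are the ones for which no supporting detail is requested. If knowledge of the arm influenced a rating, a later reader would have the questionnaire answers but not necessarily enough to re-classify the case.

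The remark on objectivity in 17a covers most of the clinically reported secondary outcomes, not all. It does not clearly extend to an outcome built on participant recall followed by an investigator's opinion. At stake is whether the trial's statement on awareness under TIVA, reassuring or alarming, can be defended when it may rest on a handful of cases.

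**Working it through.** **Denominator.** The article gives no incidence, margin or power for awareness, so there is no stated figure to reproduce for this outcome. The total of 2500 (Sample size, 14) fixes the denominator and does reproduce. With SD 7.5, difference 1 day, 5% two-sided and 90% power:

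- n per arm = 2 × (1.960 + 1.282)² × 7.5² / 1² ≈ 1183, or 2366 in total.
- Allowing 5% loss: 2366 / 0.95 = 2491, against 2500 stated.

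**Expected events.** The incidence is an assumption, taken over a range. Expected events = 2500 × rate, with all participants screened.

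| Assumed rate | Events in 2500 | Events per arm (1250) | Approx. power to detect a doubling |
|---|---|---|---|
| 0.1% | 2.5 | 1.25 | 9% |
| 0.2% | 5 | 2.5 | 15% |
| 0.5% | 12.5 | 6.25 | 30% |

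The powers use a normal approximation, which is rough at such counts.

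**Sensitivity to single ratings.** Two-sided Fisher exact test, 1250 per arm:

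| Split | p |
|---|---|
| 6 v 0 | 0.031 |
| 6 v 1 | 0.124 |
| 5 v 0 | 0.062 |
| 4 v 1 | 0.37 |
| 3 v 2 | 1.0 |

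The first two rows show the mechanism. One flagged case in the second arm, rated unlikely rather than possible, turns 6 v 1 into 6 v 0 and takes the result across 0.05. Six or seven events correspond to 6/2500 = 0.24% or 7/2500 = 0.28%, inside the assumed range. The last three rows share a total of five events. Going from 4 v 1 to either neighbour takes two reclassifications, one in each arm, and none of the three is below 0.05.

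**Sensitivity to systematic rating differences.** Suppose the true rates are equal, and the rating keeps every true case in one arm but only a fraction s in the other. The observed risk ratio is then s / 1: 0.8 if s = 80%, 0.5 if s = 50%. This holds at any incidence. The values of s are illustrative; the article gives nothing from which to estimate them.

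**What reaches the coordinating centre.** Three further places bear on this. The participant timeline (13) schedules the Brice questionnaire at day 3 and day 30 and does not mark it as a PQIP item. Data management (19) lists accidental awareness among data captured after randomisation. Section 18a specifies the additional form for two of the four ratings. Together these suggest that the answers triggering a flag are probably held centrally for everyone, while narrative detail is specified only for cases rated probable or possible.

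**The case against.** The strongest reply is that nothing is filtered out of the trial. The sentence in 18a governs one form and does not say that other Brice data are withheld. If the questionnaire answers are in the database, every flag can be counted by arm whatever the investigator thought. This stands. A reader might infer that a site investigator can rate cases out of the dataset, or that no check is possible afterwards, and the article supports neither inference. What remains is the missing supporting detail for flagged cases that were rated down.

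Second, the rating follows previously defined criteria and is not a free opinion. This also stands, as a limit on discretion. It does not supply masking.

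Third, a reader might see a contradiction with section 20a: "Quality of recovery, participant satisfaction and accidental awareness will be scored using appropriate manuals". It is a one-line summary covering three instruments and is compatible with a flag rule plus criteria. It does leave open which classification is analysed, but that detail may sit in the full protocol or the analysis plan, neither of which is shown.

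Fourth, section 22 says "the chief investigator or delegate will independently determine causality of the SAE", which might be read as a precedent for masked review. It describes a second judgement, not a masked one. It shows only that a central reader already exists.

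Fifth, with so few events the outcome is imprecise whoever classifies it, and participants are unblinded too, so bias in self-report would survive any change in classification. Both are true. Neither is a reason to leave an avoidable source of bias in place.

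**Conclusion.** The point holds in a limited form. In an open-label trial, a named safety outcome depends on a site investigator's rating made with unmasked local data, and the article specifies supporting detail only for cases that this rating puts in the upper two categories. A rating influenced by the arm could be counted around, through the raw flags, but not fully re-read.

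The size rests on an assumed incidence. At 0.1% to 0.5%, about 2.5 to 12.5 events are expected in 2500 participants, and in that range one reclassified case can move the comparison across 0.05 (6 v 1, p = 0.124; 6 v 0, p = 0.031). The article does not show that any rating was or will be biased. The full protocol may already contain an adjudication step, although the procedure that the article does set out, down to the form and the ratings that trigger it, includes none. The point does not touch the primary outcome or the sample size.

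**What to change.** In section 18a:

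1. Require the Additional Data Form for every participant flagged by the Brice rule at day 3 or day 30, with whichever of the four ratings was given recorded. The trial status section dates the end of recruitment at 10 April 2024, so in practice this means retrieving equivalent data for flagged cases before the analysis.
2. Report all rule-based flagged reports by arm as a sensitivity analysis that does not depend on the investigator's rating.
3. Have the chief investigator or delegate, who already reads SAEs centrally, classify the forms against the same predefined criteria without the allocation, as far as the case data allow.
4. State which classification is the analysed outcome, and let the wording in 20a refer to it.

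The cost is some additional forms or retrievals and a modest amount of central reading time. The article gives no flag rate, so the number cannot be stated, but it should be small. Some narratives will be harder to rate once drug details are masked, and participants' own reports remain unblinded. No sample-size figure changes.
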